### 2.10. Statistical Analysis

Statistical analysis will be performed using IBM SPSS—Mac, Version 31.0 (IBM Corporation, Armonk, NY, USA). The normal distribution of the variables will be demonstrated using the “Shapiro–Wilk” test. The analysis will be performed using an intention-to-treat (ITT) approach, and all the randomized participants will be included (including those who may discontinue the study or be noncompliant with the assigned therapy). Reasons for discontinuing the study will be recorded. Missing data will be handled through a two-stage approach. Initially, we will re-contact (recall) all participants who have incomplete data. For the remaining missing values, multiple imputation (MI) will be employed [42]. Parametric and non-parametric analyses will be performed, based on the normal distribution of the variables. A separate 2 × 3 mixed-model analysis of variance (ANOVA) will be used to examine the effects of the intervention on the primary and secondary outcomes. For the group × time interaction in the ANOVAs, the factors that will be analyzed are group (DHSG and CG) and time (baseline, end of treatment, and follow-up). For this test, a partial eta-squared (η^2^) of 0.01–0.059 represents a small effect, a value of 0.06–0.139 represents a medium effect, and a value >0.14 represents a large effect. Differences between measurements will be analyzed using Bonferroni correction. A *p*-value < 0.05 will be considered statistically significant for all the analyses.

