## Abstract

**Background:** The pediatric population with chronic suppurative lung diseases (CSLDs) presents with a clinical profile of persistent productive cough and impaired airway clearance, which leads to reduced exercise capacity and physical activity (PA). The main objective of this research is to evaluate the effect of a 12-week intervention that combines airway clearance techniques (ACTs) and exercise training delivered through synchronous (videoconferencing) and asynchronous implementation at home, supported by an informative, specially designed website and supervised by a physiotherapist on exercise capacity. The secondary objective is to assess adherence to the ACT performance. The hypothesis of the study is that this hybrid tele-rehabilitation program will improve functional and exercise capacity, as well as compliance with ACTs, compared to the usual care. **Methods**: Thirty-two children with CSLDs (other than cystic fibrosis) will be randomly assigned to either the intervention group (home-based, synchronous, and asynchronous ACTs and exercise training) or the control group (usual care). An assessor blind to group allocation will measure the modified shuttle walk test, 6-minute walking test, Chester step test, respiratory muscle strength, handgrip, pulmonary function, PA, sedentary behavior, and quality of life at baseline, at the end of the intervention (3 months), and 6 months after completion. **Discussion**: This study introduces a hybrid (synchronous and asynchronous) tele-rehabilitation program, aiming to improve physical capacity and adherence to physiotherapy management for pediatric CSLD populations.

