### 2.9. Sample Size Calculation

Due to the lack of pilot data for this specific population, the effect size was estimated a priori. We targeted a moderate effect size (f = 0.25), assuming that this represents a clinically significant improvement in exercise capacity for children with CSLDs. The required sample size was calculated with G*Power version 3.1.9.4 (G*Power, University of Düsseldorf, Düsseldorf, Germany). The “F-test” (ANOVA: repeated measures, within-between interaction) and the detection of a moderate effect size f = 0.25 (alpha level = 0.05, power = 80%) showed that a total of twenty-eight children are required. Assuming a dropout rate of 10%, the total sample size is estimated at thirty-two children, with sixteen in each group.

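### The MSWT analysis rests on a three-visit group × time interaction with no primary visit or between-group contrast fixed, and its method switches on a normality test

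*Protocol article*

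**What the plan says.** Section 2.10 (Statistical Analysis) plans that a "2 × 3 mixed-model analysis of variance (ANOVA) will be used to examine the effects of the intervention on the primary and secondary outcomes". The interaction is between group and "time (baseline, end of treatment, and follow-up"), so baseline is a level of the outcome and not a covariate. Results are graded by partial eta-squared. Bonferroni-corrected comparisons between measurements are added, but their contrasts are not defined. On the choice of method the section says: "Parametric and non-parametric analyses will be performed, based on the normal distribution of the variables". The normality check it names is Shapiro–Wilk.

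Section 2.9 (Sample Size Calculation) uses the same test, "ANOVA: repeated measures, within-between interaction", with f = 0.25, alpha 0.05 and 80% power, which "showed that a total of twenty-eight children are required". Allowing for 10% dropout brings this to 32.

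The Abstract says: "The main objective of this research is to evaluate the effect of a 12-week intervention". The Discussion states a directional hypothesis of better exercise capacity than under usual care. Section 2.7 lists three assessment times (baseline, 12 weeks, and 6 months after the intervention ends) and ranks none of them. Section 2.8.1 cites 60 m on the MSWT as a minimal clinically important difference, taken from children with cystic fibrosis.

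**The concern.** The hypothesis has a direction: the programme should do better than usual care. The omnibus interaction asks only whether the two mean profiles fail to be parallel somewhere across three visits. It gives no direction, visit or metres. A significant result could come entirely from the follow-up visit, or from a pattern that nobody would call a benefit at the end of treatment. The protocol does not call the interaction its primary test. It is, however, the only test named for intervention effects on the primary outcomes and the one used to size the trial.

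Two further matters follow. Using baseline as a response, and spending a degree of freedom on a second post-baseline visit, may cost power in a trial of 28 to 32 children. And a normality test on the variables, not on model residuals, decides which kind of analysis is run. With about 14 to 16 children per arm such a test has little power, and it leaves the choice of primary method to the data.

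**Working it through.** **Inputs.** From section 2.9: f = 0.25, alpha = 0.05, power 80%, N = 28, 10% dropout. From section 2.10: k = 2 groups and m = 3 visits. The correlation ρ between visits and the sphericity factor are not stated. I assume equal correlations and a sphericity factor of 1, and vary ρ.

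**1. The plan's own figure.** For the within–between interaction, λ = f²·N·m/(1 − ρ), with df = (k − 1)(m − 1) = 2 and (N − k)(m − 1) = 52.
- With ρ = 0.5: λ = 0.0625 × 28 × 3 / 0.5 = 10.5, power 81.2%. N = 28 is reproduced.
- Other values with m = 3 do not give 28: N = 38, 24, 18 and 12 at ρ = 0.3, 0.6, 0.7 and 0.8.
- Dropout: 28/0.90 = 31.1, which rounds up to 32 for equal arms.

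The sample size therefore agrees with the planned test, and ρ = 0.5 is the value it appears to use.

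**2. What f = 0.25 means in SD units.** Let the group differences at the three visits be (0, d, x), with 0 at baseline through randomisation. The sum of squared deviations from their mean is S = 4·m·f² = 4 × 3 × 0.0625 = 0.75.
- Fully kept (x = d) or fully lost (x = 0): S = (2/3)d², so d = √(0.75 × 1.5) = 1.06 SD.
- Half kept (x = d/2): S = d²/2, so d = √1.5 = 1.22 SD.

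**3. The test is not tied to a visit.** In general λ = (N/4)·S/(1 − ρ). Take differences of (0, 0, 1.06), so nothing at 12 weeks. Then S = 0.75, λ = 7 × 0.75/0.5 = 10.5, and the interaction is significant with probability 81%. A 12-week test would be significant 5% of the time. With 0.8 SD at follow-up only, the interaction is significant 56% of the time at ρ = 0.5 and 79% at ρ = 0.7.

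**4. Power against a single-visit ANCOVA.** The comparator is the 12-week difference adjusted for baseline, using a noncentral t with N − 3 = 25 df and residual variance (1 − ρ²)(1 + 1/(N − 4)). At ρ = 0.5 and d = 1.06, the noncentrality is 1.06/√(0.75 × 1.0417 × 4/28) = 3.17 and power is 86%.

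| N = 28, ρ = 0.5, d = 1.06 at 12 weeks | S | λ | Interaction | 12-week ANCOVA |
|---|---|---|---|---|
| Half lost by follow-up | 0.5625 | 7.875 | 68% | 86% |
| Fully kept, or fully lost | 0.75 | 10.5 | 81% | 86% |
| Grows to 1.5d at follow-up | 1.3125 | 18.375 | 97% | 86% |

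For fixed d, S is smallest at x = d/2, so the half-lost row is the worst case for the interaction.

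**5. Dependence on ρ.** With the effect fully kept or fully lost:

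| ρ | d | Interaction | 12-week ANCOVA |
|---|---|---|---|
| 0.5 | 0.8 | 56% | 63% |
| 0.7 | 0.8 | 79% | 80% |
| 0.8 | 0.8 | 93% | 91% |
| 0.9 | 0.5 | 85% | 82% |

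If d is instead set so that the interaction has exactly 80% power, ANCOVA has 80.7%, 78.4% and 76.2% at ρ = 0.7, 0.8 and 0.9. With half the effect lost, the same comparison gives ANCOVA 90.4%, 88.7% and 87.0%.

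**The case against.** The strongest reply is that the plan is coherent. It has three visits, a test over three visits, and a sample size computed for that test, which reproduces. That is correct, and I do not claim that section 2.9 is miscalculated.

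A reader might infer that the analysis contradicts a stated 12-week objective. The documents do not support this. In the Abstract, 12 weeks is the length of the intervention, not the time of the outcome, and no section names a primary visit. The defect is that none is fixed.

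A reader might also infer that the interaction always loses power. It does not. There is no gain from ANCOVA near ρ = 0.7 when the effect is fully kept or fully lost, a small loss above that, and a clear advantage for the interaction if the effect grows by follow-up.

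The Bonferroni comparisons could include a between-group contrast at 12 weeks. As worded they concern measurements, with no groups, visits or baseline adjustment specified, so they do not fix one.

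Finally, the 60 m figure comes from cystic fibrosis and is used in no objective or calculation here. The name of the rank-based alternative may also properly sit in a fuller plan. I accept both, and the point does not rest on either. The data-driven switch itself is stated in the article.

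**Conclusion.** The point holds in this form: the MSWT is analysed, and the trial sized, by a 2-df interaction that includes baseline as an outcome, with no primary visit or between-group contrast fixed. The main consequence does not depend on any power comparison. A significant result would not establish a benefit over usual care at a given visit, as the 81% figure for a follow-up-only difference shows (N = 28, ρ = 0.5, 1.06 SD).

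The loss of power is a secondary and conditional point. At ρ = 0.5 and d = 1.06 it is about 18 points at worst and about 5 points if the effect is fully kept or fully lost. With full retention or full loss it disappears near ρ = 0.7, and at ρ = 0.8 to 0.9 it becomes an advantage for the interaction of about 2 to 4 points. These figures assume equal correlations, sphericity and normal outcomes, and the protocol states no correlation. The Shapiro–Wilk switch is a separate weakness, because it makes the primary method depend on the data.

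**What to change.** - Name one primary visit. The end of treatment at 12 weeks is the natural choice.
- Make the primary analysis the between-group difference in MSWT distance at that visit, in metres with a 95% CI. Take it from an ANCOVA, or from a mixed model on the post-baseline visits, with baseline MSWT as covariate. Report the other visit as secondary.
- Replace the Shapiro–Wilk switch with checks of model residuals and a bootstrap or permutation sensitivity analysis.
- Restate section 2.9 for this contrast, with its assumed correlation.

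The cost is a change of wording and a new power calculation, to be made before outcomes are analysed. Recruitment is planned from May 2026 to May 2027, and no extra measurement is needed. The downside is slightly less power if the correlation is very high, and less power than the interaction if the effect grows after treatment ends.

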## 3. Discussion

This protocol outlines a 12-week intervention that combines ACTs and exercise training delivered through synchronous (videoconferencing) and asynchronous implementation at home, supported by an informative, specially designed website and supervised by a pediatric respiratory physiotherapist in non-CF CSLD populations.

Effective ACTs are consistently identified by both clinicians and caregivers as a fundamental component of managing CSLDs [4]. This protocol explores a hybrid digital approach to the physiotherapy management of non-CF CSLDs by integrating DHSs into everyday physiotherapy care and aiming to enhance adherence, which is often suboptimal in children and adolescents with CSLDs [43].

DHSs in pediatric respiratory care are an expanding field, aiming to provide tailored support to the special needs of this population [44]. While digital interventions have shown potential in improving pulmonary function, exercise capacity, balance, periphery, and respiratory muscle strength and HRQoL in children and adolescents with CF, with a meta-analysis reporting a mean improvement of 37.2 m in the 6MWT [15], there is limited evidence in non-CF CSLD subgroups.

The primary hypothesis is that this hybrid tele-rehabilitation program will improve exercise capacity and compliance with ACTs compared to the usual care. This hypothesis is based on the integration of synchronous supervision, which aims to maintain appropriate exercise intensity, a factor that may be compromised in conventional, unsupervised home-based care. Furthermore, the “FysAΩ” website is designed to support adherence to ACTs by providing digitized instructional resources regarding exercise and ACT performance, potentially mitigating the high non-adherence rate typically observed in pediatric CSLDs [4].

A key aspect of this study lies in its novelty, focusing on non-CF CSLD populations and expanding the existing evidence base through a rigorous methodological framework. Due to the targeted sample size, secondary outcomes beyond functional and exercise capacity (CST), as well as HRQoL, are classified as exploratory. This approach prioritizes the study’s primary objectives while exploring the preliminary impact of this hybrid tele-rehabilitation on this population. Additionally, the feasibility of the protocol is supported by the research team’s previous clinical experience in this field, participating in home-based hybrid (synchronous and asynchronous), remotely administered assessment and rehabilitation protocols in chronic diseases, using technologies such as the Vsee platform [45,46,47]. Despite this protocol referring to a single-center design, this hybrid digital structure that combines synchronous videoconferencing with an asynchronous website is designed to allow for real-time corrective feedback for ACTs while addressing geographical barriers to specialized care. Ultimately, the results of this study may contribute new insights into the integration of digital health modalities in the management of this pediatric population by physiotherapists.

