**Primary outcomes**					
Exercise capacity (MSWT)			X	X	X
Compliance (ACTs and exercise)			X	X	X

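### Airway-clearance compliance is secondary in the abstract and primary elsewhere, so the plan cannot claim 5% error and 80% power together for its two-outcome primary hypothesis

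*Protocol article*

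**What the plan says.** The protocol article gives ACT compliance two different ranks.

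- **Abstract:** exercise capacity is the main objective, and "The secondary objective is to assess adherence to the ACT performance".
- **Section 2.8.1**, whose heading refers to a primary outcome in the singular, has two subsections: the MSWT, and compliance with ACTs and the exercise program. Secondary outcomes start only at 2.8.2.
- **Table 1:** the block of primary outcomes has one row for the MSWT and one for "Compliance (ACTs and exercise").
- **Discussion:** "The primary hypothesis is that this hybrid tele-rehabilitation program will improve exercise capacity and compliance with ACTs compared to the usual care".

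Section 2.9 sizes the trial with one test ("ANOVA: repeated measures, within-between interaction") and one effect size, f = 0.25, "assuming that this represents a clinically significant improvement in exercise capacity for children with CSLDs". The calculation "showed that a total of twenty-eight children are required", raised to 32 for 10% dropout. No effect size is given for compliance.

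Section 2.10 plans a separate group-by-time ANOVA for each primary and secondary outcome, and a p-value below 0.05 "will be considered statistically significant for all the analyses". Its Bonferroni correction is stated for differences between measurements and not across outcomes.

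**The concern.** The rank of compliance decides what counts as a successful trial. Suppose the MSWT shows no effect and the ACT diary favours the intervention. Under the abstract, the main objective has failed. Under Table 1, a primary outcome has been met. The article supports both reports.

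That result is plausible. Families cannot be blinded, and the diary is completed through the website in the intervention arm but by telephone with a physiotherapist in the control arm. The intervention arm also receives weekly reminders. Compliance with the exercise program is recorded in the intervention arm only, so that part of the Table 1 row has no control comparison.

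The stated error rate and power were set for one test on one outcome. A primary hypothesis about two outcomes needs a rule for combining them, and the rule determines which of the two properties still holds.

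**Working it through.** **Inputs.** From 2.9: alpha 0.05, f = 0.25, power 80%, N = 28 evaluable, dropout 10%. From 2.10: k = 2 groups, m = 3 time points, p < 0.05 for each analysis. Assumed, because the article gives neither: correlation between repeated measurements rho = 0.5, and sphericity (epsilon = 1).

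**1. The plan's own figure.** For the group-by-time interaction, the noncentrality is f² × N × m / (1 − rho) = 0.0625 × 28 × 3 / 0.5 = 10.5. The degrees of freedom are (k − 1)(m − 1) = 2 and (N − k)(m − 1) = 52. Power is 81.2%, and 28 is the smallest even N that reaches 80%. Dropout: 28 / 0.9 = 31.1, rounded up to 32. Both stated numbers reproduce. They depend on rho: at 0.3 the required N is 38, and at 0.7 it is 18.

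**2. Either outcome suffices, each tested at 0.05.** If the tests are independent, the chance of at least one false positive is 1 − 0.95² = 9.75%. With correlated two-sided normal test statistics:

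| Correlation between outcomes | Error rate |
|---|---|
| 0 | 9.75% |
| 0.3 | 9.5% |
| 0.5 | 9.1% |
| 0.7 | 8.3% |
| 0.9 | 7.0% |

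Power to win on at least one outcome is no lower than the MSWT's own 81.2%, provided the assumed MSWT effect is real.

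**3. Both outcomes required, each tested at 0.05.** A false claim needs a rejection on an outcome with no effect, so the error rate is at most 5%. Joint power cannot exceed the 81.2% for the MSWT. To illustrate, give compliance the same f = 0.25 and rho = 0.5. If the outcomes are independent, joint power at N = 28 is 0.812² = 66%. Simulation of the two interaction tests (40,000 runs) gives 68%, 70% and 74% at between-outcome correlations of 0.3, 0.5 and 0.8.

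**4. Sizes under each choice** (the two-primary rows carry the same illustrative assumptions for compliance):

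| Choice | Power at 28 evaluable | Needed for 80% |
|---|---|---|
| MSWT sole primary, alpha 0.05 | 81% | 28 evaluable, 32 randomised |
| Either suffices, alpha 0.025 each | 72% per outcome | 34 per-outcome evaluable, 34/0.9 → 38 randomised |
| Both required, alpha 0.05 each, independent | 66% jointly | 36 evaluable, 36/0.9 = 40 randomised |

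**The case against.** The body of the article largely agrees with itself: section 2.8.1, Table 1 and the Discussion all treat compliance as primary. Even the abstract's hypothesis sentence names both outcomes. On this view only the abstract's ranking of objectives is out of line. That narrows the conflict but does not remove it, because section 2.9 sides with the abstract by sizing on exercise capacity alone.

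A journal article may leave the decision rule for two primaries to the full protocol or the analysis plan, and p < 0.05 throughout is compatible with a both-required rule, which needs no split of alpha. This stands: the unstated rule is not an error by itself. But no later document can supply a rule without first overruling either the abstract or the other three places.

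The joint-power figures are a scenario. The article gives no effect size, standard deviation or correlation for compliance. With power of about 98.5% for compliance, joint power would be about 80% even under independence (0.812 × 0.985 = 0.80). This also stands: the 80% has not been shown to hold for the joint claim, which differs from showing that it fails.

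A reader might infer that neither the 5% error rate nor the 80% power applies to the primary hypothesis. The documents do not support that. Requiring both outcomes keeps the error rate at or below 5%. Accepting either keeps at least the MSWT's power. Each rule puts only one of the two properties in doubt.

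**Conclusion.** The conflict over the rank of compliance is certain from the text and should be settled before recruitment, which is planned to start in May 2026. While it stands, the article cannot claim 5% error and 80% power together for its two-outcome primary hypothesis. Accepting either outcome raises the error rate to between 7.0% (correlation 0.9) and 9.75% (independence). Requiring both leaves joint power capped at the MSWT's own and unsupported at 80%, with 66% to 74% as an illustration.

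The error rates rest only on two tests at 0.05 and a range of correlations. The power figures also rest on rho = 0.5, sphericity and a borrowed effect size for compliance. The sample size calculation itself is sound for a single exercise-capacity outcome under that rho.

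**What to change.** **Preferred: one primary outcome.** Keep the MSWT as the single primary outcome, since it matches the main objective in the abstract and the outcome sized in 2.9. Move compliance to the secondary outcomes in 2.8 and Table 1. Limit the primary hypothesis in the Discussion to exercise capacity. Say in 2.9 that the 80% power applies to the MSWT only. Check that the registry entry agrees. The 28 evaluable and 32 randomised stand, so no extra children are needed. The costs are that compliance alone can no longer carry a primary claim, and that a registered primary outcome may have to be amended before recruitment. The registry entry was not available for this review.

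**Alternative: two primary outcomes.** Correct the abstract, state whether both or either must succeed (splitting alpha if either), give an effect-size assumption for compliance, and restate the power. Under the illustrative assumptions above, 80% would need 38 randomised (either, 0.025 each, per outcome) or 40 randomised (both, independent), against the planned 32.

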## Figures and Tables

**Figure 1 healthcare-14-01250-f001:**
[figure not shown]
Study flow chart.

**Table 1 healthcare-14-01250-t001:** Standard protocol items: recommendations for interventional trials (SPIRIT) 2025.

	Enrollment	Allocation	Baseline	12 Weeks	6 Months
